#### Efficacy Analyses

Analyses of all outcomes will also be conducted on a per-protocol basis to test the efficacy of different doses under “ideal” conditions of high compliance. The model will incorporate study visit (T0, T0.5, and T1; additional analyses will include T2) and intervention (10, 20, and 30 min each vs the minimal dose) as categorical variables. The per-protocol analysis sample will consist only of those participants who were compliant with the allocated intervention dose, excluding those who did not comply as opposed to reallocating them to an arm representing their actual dose. A “complier” will be defined by having reported session completion for >66.67% and <117% of sessions (100%=6 weekly sessions=24 sessions).

Estimation of effects in randomized controlled trials is known to be biased when there are variable rates of nonadherence to treatment [58]. To control for prerandomization factors that may influence nonadherence to the 10-, 20-, and 30-minute conditions, we will adjust for prerandomization confounders for the per-protocol analysis, such as personality traits (conscientiousness [59,60]), openness to experience [59,61], depressive symptoms [59,61], and motivations and expectations [60]. The method of inverse probability weighting will be used to control for confounding bias due to prerandomization factors [62]. A causal diagram will be drawn to determine a priori potential pre- and postrandomization confounders associated with being a complier [58].

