This study is being conducted entirely online. This has the advantage of allowing participants to practice in their homes and other familiar ecologically valid settings, although it also has the limitation of researchers having little control over the research environment. However, a common problem with internet-based interventions is high dropout rates and low adherence. Our primary analysis is to test the effectiveness of different doses, and therefore, our data will be analyzed on an intention-to-treat basis. As such, we are most concerned with the problem of high dropout rates. To minimize dropouts, we are offering financial inducements for participants to continue honestly reporting their practice amount and responding to questionnaires regardless of whether they are still completing the intervention. However, it is still in our interest to have high rates of adherence given that we will also analyze data on a per-protocol basis (ie, as secondary analyses only). To this end, we are using a run-in period to identify and exclude participants who are most likely to drop out and not complete the intervention before randomization. Given this use of the run-in period, we cannot make inferences about the likely adherence to similar mindfulness interventions in real-world settings. Therefore, while the use of a run-in period strengthens internal consistency, it introduces a selection bias. We will attempt to quantify this by reporting sociodemographic data and measures of mental health and well-being for people that complete the run-in period and compare them against those of people who do not. Despite the use of a run-in period, we still anticipate that adherence rates are likely to vary across dosage groups, with lower adherence at higher doses. This may limit our capacity to make inferences about the efficacy of different doses for the per-protocol analyses.

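### The per-protocol plan will look for post-randomization confounders of compliance, but the only adjustment it states covers pre-randomization factors

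*Protocol article*

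**What the plan says.** All of this is in the protocol article.

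- **Sample** (Efficacy Analyses): "The per-protocol analysis sample will consist only of those participants who were compliant with the allocated intervention dose". Non-compliers are dropped, and no arm is exempt.
- **Complier rule** (Efficacy Analyses): "defined by having reported session completion for >66.67% and <117% of sessions", where 100% is 24 sessions.
- **Model** (Efficacy Analyses): "intervention (10, 20, and 30 min each vs the minimal dose) as categorical variables", so the 4-minute arm is the comparator.
- **Motive for adjusting** (Efficacy Analyses): "To control for prerandomization factors that may influence nonadherence to the 10-, 20-, and 30-minute conditions".
- **Adjustment** (Efficacy Analyses): "The method of inverse probability weighting will be used to control for confounding bias due to prerandomization factors".
- **Next sentence** (Efficacy Analyses): "A causal diagram will be drawn to determine a priori potential pre- and postrandomization confounders associated with being a complier".
- **Expectation** (Strengths and Limitations): "adherence rates are likely to vary across dosage groups, with lower adherence at higher doses". The authors add that this may limit per-protocol inference.
- **Status** (General Principles): per-protocol analyses are secondary; the primary analysis is intention-to-treat.

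**The concern.** The diagram is to find confounders on both sides of randomization, but the weights deal with one side only. Compliance builds up over four weeks. Early benefit, an adverse experience or a judgement that the course is not working could each affect whether a participant carries on, and also the T1 well-being score. Weights built from baseline variables cannot remove that.

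The amount of selection is expected to differ by arm, because adherence is expected to fall with dose. Any leftover selection would therefore fall unevenly across the arms and could be mistaken for a dose effect, or could hide one. The per-protocol analysis is presented as the test of efficacy under high compliance for every outcome. Under Additional Analyses, a difference in any primary or secondary analysis opens the way to linear and log-linear dose-response models, so an artefact here could carry further.

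A smaller point concerns the arms. The sentence giving the motive names only the three longer doses, although the complier restriction and the contrasts also involve the 4-minute arm.

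**Working it through.** **1. When complier status is fixed.** 66.67% of 24 = 16.0008 and 117% of 24 = 28.08, so a complier reports 17 to 28 sessions. The rule is the same in every arm and is cumulative. For example, 0 sessions in week 1 and 6 in each later week gives 18, which is a complier.

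**2. The plan's own figures.** The target difference is 0.2 × 9.84 = 1.97 points. The change-score SD is 9.84 × √(2 × (1 − 0.83)) = 5.74. With two-sided α = 0.02 and 80% power, n = 2 × (2.326 + 0.842)² × 5.74² / 1.97² gives 171 per arm and 684 in total. The plan states 688, so 5.74 is consistent with its calculation.

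**3. Illustration A: one post-randomization factor.** None of these inputs is in the document:
- no true dose effect
- compliance of 80% at 4 minutes and 50% at 30 minutes
- logistic compliance, with odds ratio (OR) 1.5 to 2.0 per SD of early response L
- correlation ρ of 0.3 to 0.7 between L and the T1 change

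Mean change among compliers = ρ × 5.74 × E[L | complier]. By numerical integration:

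| OR, ρ | 4 min (80%) | 30 min (50%) | Difference | Share of 1.97 |
|---|---|---|---|---|
| 1.5, 0.3 | 0.14 | 0.34 | 0.20 | 10% |
| 2.0, 0.7 | 0.52 | 1.26 | 0.74 | 37% |

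If early responders are instead more likely to stop (OR 1/1.5 to 1/2.0), symmetry gives −0.20 to −0.74.

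**4. Illustration B: what baseline weights leave behind.** Also assumed throughout:
- T1 score in SD units = 0.3C + 0.4L + noise, where C is a pre-randomization and L a post-randomization factor
- logit of compliance = a + s(C + L), with (a, s) = (2.0, 0.3), (1.2, 0.5), (0.6, 0.7) and (0, 0.9) from 4 to 30 minutes
- resulting compliance of about 87%, 75%, 62% and 50%
- no true dose effect

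Spurious 30- versus 4-minute difference in points, by numerical integration:

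| Analysis | L raises compliance | L lowers compliance | L irrelevant to compliance |
|---|---|---|---|
| Unweighted | +2.10 | −0.30 | +1.02 |
| Weights on C, four arms | +1.38 | −1.38 | 0.00 |
| Weights on C, 4-minute arm unweighted | +1.27 | −1.49 | −0.11 |

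A simulation of 400,000 per arm gives +1.40 and +1.29 for the two weighted entries in the first column, and 0.00 once L enters the weights. Baseline weights are sufficient only in the last column.

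**5. The 4-minute arm.** If that arm were left unweighted at 80% compliance, the mean baseline trait among its compliers would be 0.079 SD (OR 1.5) or 0.129 SD (OR 2.0). With a trait effect of 0.1 to 0.2 SD on T1 well-being, the shift runs from 0.079 × 0.1 × 9.84 = 0.08 to 0.129 × 0.2 × 9.84 = 0.25 points. Illustration B gives about 0.1.

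**6. Which covariates could enter, and when.** Suppose sessions are counted from the weekly item, which runs from 0 to 7. Four weeks at 7 is 28, so the upper end of the band cannot be exceeded. The lower end is out of reach:
- after week 2, with fewer than 17 − 14 = 3 sessions
- after week 3, with fewer than 17 − 7 = 10
- after week 4, with fewer than 17

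Nobody can fail the rule in week 1. Week 1 measures can inform week 2, and T0.5 measures can inform weeks 3 and 4 only.

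**The case against.** **Only one adjustment is stated.** The diagram sentence describes identification and does not say what enters the weights. An article may leave the weight model to an analysis plan that is not shown. This stands as far as missing detail goes. It does not explain why post-randomization confounders are to be identified when the stated weighting is confined to pre-randomization factors.

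**Three stronger readings are tempting but unsupported.**
- A reader might infer that the 4-minute arm will go unweighted. The list of three doses appears only in the clause giving the motive. The weighting sentence names no arms, and the adjustment is announced for the per-protocol analysis as a whole. Even on that reading the effect is small.
- A reader might conclude that compliers will not be comparable across doses. That fails if no post-randomization factor drives both compliance and outcome. The document supports only that comparability is not secured.
- A reader might expect per-protocol means to rise with dose and imitate the first hypothesis. That needs early responders to be likelier to stay. The document says only that adherence falls with dose, and participants who feel better early might equally stop.

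**The consequence is limited and partly disclosed.** The analysis is secondary, and the authors warn that differential adherence may limit it. That lowers the weight of the point, but the warning does not say which confounders are adjusted for.

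**Post-randomization weights are awkward here.** Weekly on-schedule weights would model a different event from the cumulative rule. The primary outcome is not measured at T0.5, so early well-being response is seen only through proxies. The T0.5 distress scale looks back a month and overlaps the period before randomization. These objections stand and shape the fix.

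**Conclusion.** The point holds as a mismatch within Efficacy Analyses: post-randomization confounders of compliance are to be identified, and the stated weighting does not cover them. With compliance determined after randomization and expected to fall with dose, baseline-only weights do not secure comparability of compliers across doses if a post-randomization factor affects both compliance and T1 well-being.

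The document fixes neither the direction nor the size of any bias. Under the assumed inputs the 30- versus 4-minute contrast moves by 0.20 to 0.74 points (10% to 37% of the target) in Illustration A. About 1.4 points (some 70% of 1.97) remain after baseline weighting in Illustration B. Either sign is possible, and the bias is zero if pre-randomization factors suffice. The wording about arms needs clarifying and is worth at most about 0.25 points under the stated assumptions. The primary intention-to-treat analysis is untouched. This should be corrected before the per-protocol analysis is run.

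**What to change.** In Efficacy Analyses:

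1. State that complier weights are estimated in all four arms, including the 4-minute arm.
2. Extend the weights to post-randomization covariates already collected: weekly adverse events, sleep and perceived effectiveness, and the T0.5 secondary measures for weeks 3 and 4 only. Keep the weights consistent with the cumulative rule, for example by censoring a participant in the week when the 17 to 28 session band can no longer be met. Report baseline-only weights alongside.
3. If step 2 is not adopted, state plainly that the per-protocol estimate assumes no post-randomization confounding of compliance.

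No new data are needed; the cost is wording and programming. The drawbacks are more variable weights, wider per-protocol intervals, and weekly survey covariates that may be missing and need a stated rule. Settling this in advance also removes a later choice between adjustment sets.

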#### Additional Analyses

If any difference between any conditions is observed for any of the primary or secondary analyses, we will explore ways of quantifying that relationship as a means of representing dose-response effects. In particular, we will test for the presence of a linear and log-linear relationship across the treatment doses.

We will describe differential rates of attrition and adherence across the different treatment arms and explore whether any variables collected at baseline predict differential attrition and adherence.

Using estimated practice time per adherence measures, we will implement a receiver operating characteristic analysis to ascertain the practice amount at which individuals achieve a change of ≥7.45 points on the primary outcome of the WEMWBS (estimated temporal SE of measurement of 2.69 [35] using a multiplier of 2.77 [63]) to detect a statistically important change at the individual level.

Further exploratory analyses will be conducted using both the intention-to-treat and per-protocol approaches on outcomes collected at weekly and biweekly intervals.

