### Sample Size

A meta-analysis of meditation apps [1] indicates a standardized mean difference (SMD) effect size of 0.29 (95% CI 0.14-0.45) for psychological well-being when comparing apps to controls. A more recent study [6] randomized participants to approximately 10 or 30 minutes of sitting or movement practice for 2 weeks. They estimated a difference in the effects on the WEMWBS between the sitting groups of short and long duration of SMD=0.2 to 0.25. To be conservative, we determined a target sample size with an SMD of 0.2.

On the basis of an SD in WEMWBS scores of 9.84 [55] and a within-individual correlation of 0.83 in repeated assessments of the WEMWBS [34], we would need a final sample size of 688 participants to achieve 80% power (at the 2-sided *P*=.02 significance level to correct for multiple comparisons between conditions) to detect a difference of 1.97 points (SMD=0.2) for each active condition (10, 20, and 30 min) compared to one another and with the minimal-dose condition. This would translate to approximately 172 participants per arm. These calculations were conducted using the *sampsi* package in Stata (StataCorp).

Meditation app studies indicate overall retention rates of approximately 60% for active mindfulness meditation interventions [1]. Given our use of a run-in period, the aim of which is to allow participants who are most likely to disengage to do so before randomization, we anticipate postrandomization retention rates approximating 80%. In total, we will then recruit on a rolling basis until we achieve the required sample size at randomization of 860.

We will aim to recruit the full sample by March 31, 2025. We will conduct an interim analysis at this stage if the sample is at <90% of the target. If the sample is at ≥90% of the target by March 31, 2025, recruitment will be terminated. If continued recruitment is necessary (ie, we recruit <90% of the sample by March 31, 2025), recruitment will continue until the target sample is reached or 6 months (from March 31, 2025) have elapsed (whichever occurs first). If an interim analysis is required, the team member who undertakes this analysis will not implement the final analysis (as they will need to be unblinded). Other members of the team will undertake the final analysis and will alter the arm designation in the analytic code to further blind results relative to the interim analysis.

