Given our focus on the question of dose-response effects, our analysis examines the effectiveness of different doses relative to each other (and to a minimally active control). Therefore, we cannot make inferences about the effectiveness of the intervention relative to other psychosocial interventions. However, the intervention shares several characteristics that align with the definition of MBPs by Crane et al [30]. Therefore, we are relying on this evidence base, which has demonstrated the effectiveness of similar MBPs, while focusing on one aspect of such programs that is less empirically validated, namely, whether and to what degree shorter or longer daily practices are more beneficial.

All outcome data are self-reported, introducing the potential for recall bias, social desirability bias, and inaccuracies. Despite these limitations, self-report measures were chosen for their practicality and suitability for collecting data online for well-being, the primary outcome, and various secondary outcomes.

Finally, we are tracking and will follow up on reports of adverse experiences throughout the intervention and follow-up periods. Britton [67] has hypothesized that meditation-related adverse experiences and problems with sleep may be more likely to occur at higher doses. While our dosage may still be relatively low compared to that of high-dose settings such as residential retreats, our study design will allow us to explore the question of whether and when higher doses of mindfulness may be riskier than lower doses.

Considering these strengths and limitations, our study will make a significant contribution to the growing literature on the dose-response effects of mindfulness meditation, providing much-needed empirical support to the question of whether and when larger doses are more beneficial than smaller ones. These findings may inform practical guidelines, helping beginner meditators and their advisors—whether in health, well-being, or spiritual contexts—estimate the amount of practice required to achieve particular outcomes.

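### The exploratory practice-amount analysis splits WEMWBS change at 7.45 points and seeks a ROC cut-off; no stated analysis relates practice time to the full WEMWBS scale, so information is lost and the cut-off will be unstable

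*Protocol article*

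**What the plan says.** All references are to the protocol article.

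- **Additional Analyses.** Practice time is to be estimated from what participants report about adherence. For WEMWBS change the text then reads: "we will implement a receiver operating characteristic analysis to ascertain the practice amount at which individuals achieve a change of ≥7.45 points". The threshold rests on an "estimated temporal SE of measurement of 2.69"; the factor applied to it is described as "using a multiplier of 2.77". It is meant to mark change in an individual. The section gives no hypothesis, significance level, power or rule for choosing the cut-off.
- **Effectiveness Analyses and Additional Analyses.** The primary model keeps WEMWBS continuous and compares assigned arms. The linear and log-linear tests also use treatment dose rather than practice time, and are run only if some difference between conditions is seen.
- **Sample Size.** The inputs are "an SD in WEMWBS scores of 9.84" and, for the correlation, a "within-individual correlation of 0.83 in repeated assessments of the WEMWBS". The target difference is 1.97 points, with 172 participants per arm and 688 in total.
- **Strengths and Limitations.** The study's findings may help beginners and their advisors "estimate the amount of practice required to achieve particular outcomes".

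**The concern.** The ROC analysis is the only stated analysis that turns practice time into an amount. It reduces a continuous outcome to responder or non-responder and then seeks a single point on the practice scale. Participants who change by 7 points and those who do not change at all count the same. The 7.45 cut also lies well into the upper tail of the change distribution that the plan's own figures imply, so responders are a minority and carry most of the information.

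Two things are at stake. A real association between practice and well-being could be missed in data able to show it. And a practice amount could be reported that a repeat of the same trial would place somewhere quite different.

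**Working it through.** **The plan's own figures.**
- Threshold: 2.69 × 2.77 = 7.4513, and 1.96 × √2 = 2.77. The 7.45 reproduces as a reliable-change limit.
- SD of change: 9.84 × √(2 × (1 − 0.83)) = 5.74.
- Sample size: 1.97 points, SD 5.74, 80% power and 2-sided .02 give 171 per arm against the stated 172. Then 688 / 0.80 = 860. Both reproduce.

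**Where the cut lies.** 7.45 / 5.74 = 1.30 SDs of change above zero. With normal change scores, the share reaching 7.45 is 1 − Φ((7.45 − mean) / 5.74):
- mean change 0: 9.7%
- mean change 1.97: 17.0%
- mean change 4: 27.4%
- mean change 5: about 34%

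The article gives no mean change, so these means are assumptions.

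**Role of baseline.** With r = 0.83, mean change 0 and no effect of practice, about 17% of the lowest baseline quartile reach 7.45, against about 4% of the highest. The residual SD of T1 given baseline is 9.84 × √(1 − 0.83²) = 5.49.

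**Simulation of the practice-time analysis.** Inputs:
- From the article: 4 arms of 172; doses of 4, 10, 20 and 30 minutes; 24 guided sessions; SD 9.84; correlation 0.83; effect 1.97.
- Assumed: sessions completed follow 24 × Beta(4, 1.5), a mean of 24 × 4/5.5 = 17.5 sessions or about 73%; overall mean change 0 to 4 points; a linear or log relation, with 1.97 points between the 4- and 30-minute doses at mean adherence; 2-sided .05; ROC cut-off chosen by the Youden index.

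The Mann-Whitney (ROC-area) test of minutes by responder status was compared with regression of T1 on baseline and practice.

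- **Power at 1.97 points:** about 53 to 79% for the ROC area and 96 to 99% for the regression. Matched scenario by scenario, the loss is roughly 20 to 45 points. It is largest at mean change 0, where responders are rarest.
- **Stronger association:** with 3 points between the same doses the loss is about 0 to 12 points.
- **Cut-off:** the 5th to 95th percentile range is about 90 to 480 total minutes across these scenarios. With no practice effect at all, the method still returns a cut-off, with a median of about 220 minutes and a range of about 53 to 640.

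**Sensitivity to the assumptions.** These runs used a different adherence distribution, Beta(2.5, 1.2), a mean change of 0 or 2 points at the reference dose, and an unadjusted correlation of minutes with change as the comparator.
- With 1.97 points between the 4- and 30-minute doses, the practice-change correlation is about 0.11 to 0.15 and the loss 18 to 36 points.
- With error in reported practice time (SD 0.5 on the log scale), the loss is 12 to 25 points, because the continuous test weakens too.
- At half the effect, without that error, the loss is 13 to 17 points.
- If every step between adjacent doses were worth 1.97 points, the correlation is about 0.30 and the loss is nil.
- At a correlation of 0.26, power loss is 0 to 1 point, but the 95% range of the cut-off is still about 6.6 to 18 minutes per scheduled session.

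**The case against.** The strongest reply is that no planned test loses power. The ROC analysis is one of several additional analyses, has no stated hypothesis or significance level, and aims to describe. The primary, secondary, per-protocol and dose-trend analyses do not use the cut. This stands, and limits the point to an optional improvement.

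Three stronger readings are tempting and are not supported.

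- **A fixed loss of power.** A reader might compare two arms of 172 on responder rates at .02 (36% against 80% for continuous change) and take the gap as the trial's loss. The plan contains no such comparison, and the .02 level belongs to the primary outcome. For the practice-time analysis, the loss depends on an unknown strength of association and mean change. The only practice-outcome correlation in the article (0.26, in Background and Rationale) would make it almost vanish, though that figure concerns anxiety, depression and stress rather than WEMWBS.
- **The cut-off as the trial's guidance figure.** The closing sentence of Strengths and Limitations refers to the findings of the whole study, not to this cut-off.
- **An arbitrary or unadjusted cut.** The 7.45 is prespecified and derived from a reliable-change rule, and individual change is a legitimate question. The article does not rule out baseline adjustment or intervals, and does not name the Youden rule. A condensed article may leave these to the analysis plan.

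One limit applies equally to the alternative: achieved practice is self-selected. Regression estimates the association more precisely but does not make it causal.

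What remains is that the ROC analysis by construction uses a yes/no outcome, that no full-scale practice-time analysis is stated beside it, and that the cut-off is imprecise even where the power loss is small.

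**Conclusion.** The point holds as a modest, low-cost improvement to an exploratory analysis. With 1.97 points between the 4- and 30-minute doses, the assumed adherence and a mean change of 0 to 4 points, splitting the outcome costs roughly 20 to 45 points of power against baseline-adjusted regression. It costs about 0 to 12 points if the association is stronger, and less than the main range if practice time is poorly reported or the effect is smaller. Placing the 1.97 points between the extreme doses is itself an assumption, since the sample-size text applies that difference to every pair of conditions.

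The instability of the cut-off is the firmer part: about 90 to 480 total minutes in the main scenarios, still wide at a correlation of 0.26, and a value is returned even when practice has no effect. No powered hypothesis, and no conclusion about assigned dose, is affected.

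**What to change.** In Additional Analyses:

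1. Make the main practice-amount analysis a regression of T1 WEMWBS on baseline WEMWBS and practice amount, with a linear, log or spline form.
2. From the fitted mean and residual distribution, report the estimated probability of a change of at least 7.45 points at each practice amount, with bootstrap 95% confidence intervals. This keeps the individual-change question and the prespecified threshold.
3. Keep any ROC cut-off only as a descriptive supplement with a bootstrap interval.
4. Describe both results as associations, because achieved practice is not randomised.

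The cost is a change of wording and a little more analysis code on the same data. The downside is that a curve with an interval replaces one headline cut-off, and that the derived probabilities rely on the residual distribution, which can be checked.
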